## **Plan for addressing confounding**

We plan to adjust for the following confounding factors: sex, age, ethnicity, socioeconomic status using the Practice/Patient Level Index of Multiple Deprivation.

## **Plans for addressing missing data**

We will use complete case analysis for missing data for all demographic analyses. As a sensitivity analysis we will compare results using complete case analysis with results derived using multiple imputation with chained equations. The number of imputed datasets will be determined through the Fraction of Missing Information (FMI) statistic. Both sets of analyses will be reported.

## **Patient or user group involvement**

No patients will be involved in this research at this stage. There are no plans to disseminate this proposal to patients' groups at this stage.

## **Plans for disseminating & communicating**

The authors are planning to disseminate the study results through peer-reviewed journals, academic conference presentations, the Scottish Government, key stakeholders and policy makers communication channels, the Scottish Learning Disabilities Observatory website, newsletter and social media. There are no restrictions on the extent and timing of publication.

## Conflict of interest statement

None

## Limitations of study design

Practice-based deprivation measure may not represent individual-level socioeconomic status. Information on the socioeconomic status of patients is available for English practices only, which may limit the generalisability of our findings. There may also be an under-representation of people with intellectual disabilities and co-occurring challenging behaviours in the dataset, as there may be a significant number of patients without a formal diagnosis. Errors and inconsistencies in recording challenging behaviours may present problems in data quality. There may also be unrecorded or unreported physical conditions in the population with intellectual disabilities in the primary care data. In investigating the association of specific physical conditions with challenging behaviours, we may be limited to analysing more common physical conditions only due to small sub-sample sizes. Variation in coding across different practices and over time may introduce systematic biases. Linkage to the HES Admitted Patient Care and Mental Health Services Data Set (MHSDS) may limit the sample size, depending on the quality of the linked data.

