## **Data/statistical analysis**

The analysis will be performed using STATA/SPSS Software. In our main analyses, patients will be stratified into subgroups by age, sex and co-occurring intellectual disabilities. All of the analyses as described below will be performed for each subgroup.

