### **Phase 2**

The main statistical analyses will be conducted using stratified Cox proportional hazard models (Sjolander & Greenland 2013). The Cox models will be run univariately, then multivariably. The multivariable analysis will comprise (i) adjustment for demographic (age, gender, ethnicity) and socioeconomic (Practice/Patient Level Index of Multiple Deprivation) factors, (ii) the addition of mediators (i.e. severity of intellectual disabilities, co-occurring autism/genetic syndromes/mental comorbidities) factors) to the above model to assess any attenuation in the associations (iii) the use of likelihood ratio tests to test for interaction effects with the effect modifier (i.e. physical conditions including pain, sleep problems, constipation, epilepsy, urinary/bowel incontinence and sensory impairments) if there is sufficient statistical power and if found to be statistically significant, further sub-group analyses. We will test for proportional hazards in the Cox models using both graphical methods and a formal statistical test based on Schoenfeld residuals. Where the assumption of proportional hazards is violated, we will augment the models with time varying covariates. To account for patients with multiple events over the 10-year study period and investigate incidence rate ratios, we will conduct a Poisson regression, similarly to the methodology applied by Sheehan et al. (2015).

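### The protocol names coding variation between practices and over time as a possible bias, but its listed adjustment set and named strata include neither practice nor calendar period

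*Protocol*

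**What the plan says.** The limitations section of the protocol (Limitations of study design) states: "Variation in coding across different practices and over time may introduce systematic biases".

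The analysis sections then set out the following.

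- **Adjustment.** The confounding section reads: "We plan to adjust for the following confounding factors: sex, age, ethnicity, socioeconomic status using the Practice/Patient Level Index of Multiple Deprivation". Phase 2 repeats this as "adjustment for demographic (age, gender, ethnicity) and socioeconomic (Practice/Patient Level Index of Multiple Deprivation) factors". It then adds severity of intellectual disabilities, autism, genetic syndromes and mental comorbidities, and after that the interaction tests.
- **Strata.** Phase 2 says: "The main statistical analyses will be conducted using stratified Cox proportional hazard models". It does not say what the strata are. The opening of the analysis section says that "patients will be stratified into subgroups by age, sex and co-occurring intellectual disabilities".
- **Time.** Phase 2 says: "Where the assumption of proportional hazards is violated, we will augment the models with time varying covariates". Calendar period is not mentioned.
- **Repeated events.** For patients with several events, "we will conduct a Poisson regression". No practice or period term is given.

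The outcomes section and the exposures section identify both the physical conditions and the challenging behaviours by Read codes in the primary-care record.

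**The concern.** Research question 2 asks whether physical conditions raise or lower the incidence of challenging behaviours. Both sides of that comparison are recorded events. A practice that codes thoroughly may record more constipation, more sleep problems and more challenging behaviour in the same kind of patient. Practice is then a common cause of recorded exposure and recorded outcome. The only practice attribute that could enter the model is practice-level deprivation, which measures deprivation and not coding.

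Calendar time matters too. The first aim is to describe trends in incidence, follow-up runs from 2009 to 2019, and entry is staggered. A drift in coding over those years would act directly on the trend, and would act on the association if both kinds of code drift together.

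The protocol classes the study as hypothesis testing and argues its power from sample size alone. A large sample does not shrink a recording bias; it makes a spurious ratio more likely to reach significance.

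**Working it through.** **1. The protocol's own figures.** Both reproduce from the sample-size section: 16,305,791 × 0.005 = 81,528.96 (stated 81,529), and 81,529 × 0.165 = 13,452.3 (stated 13,452). The section gives no target effect, between-practice variance or design effect, so the size of the bias has to rest on assumptions.

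**2. Practice size.** The earlier studies cited under feasibility give 21,859 / 451 = 48.5 and 14,751 / 408 = 36.2 adults with intellectual disabilities per practice.

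**3. Model for the bias.** Take a true ratio of 1. Let the log-odds of a recorded condition in a practice be a + s·u, and let the recorded outcome rate be proportional to exp(s·v). Here u and v are standard normal with correlation ρ. Exposed patients come from practices whose mean u is higher by about s, so their mean v is higher by about ρs and their mean log rate by about ρs². Hence

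false ratio ≈ exp(ρs²).

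Assumed inputs: about 20% of patients with the condition recorded (a = −1.4), s = 0.2 to 0.5, ρ = 0.5 to 1.

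| s | ρ | exp(ρs²) | exact under this model |
|---|---|---|---|
| 0.2 | 0.5 | 1.020 | 1.020 |
| 0.2 | 1 | 1.041 | 1.041 |
| 0.3 | 0.5 | 1.046 | 1.045 |
| 0.3 | 1 | 1.094 | 1.093 |
| 0.5 | 0.5 | 1.133 | 1.127 |
| 0.5 | 1 | 1.284 | 1.271 |

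At ρ = 0 the ratio is 1.00. At negative ρ it falls below 1.

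**4. Does practice stratification help?** A simulation used 451 practices of 48 patients, 10 years of follow-up, an assumed 1.65% event rate per year and 400 runs per setting. It compared the crude rate ratio with one stratified by practice (Mantel-Haenszel). Rejection is at nominal 5%.

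| s | ρ | crude ratio | crude, rejected | crude with clustered SE, rejected | practice-stratified ratio | practice-stratified, rejected |
|---|---|---|---|---|---|---|
| 0.3 | 0.3 | 1.03 | 9% | 9% | 1.00 | 3% |
| 0.5 | 0.3 | 1.07 | 43% | 39% | 1.00 | 5% |
| 0.5 | 0.5 | 1.13 | 83% | 80% | 1.00 | 5% |

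Practice strata remove the false association. Clustered standard errors do not, because the estimate itself is shifted.

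**5. Calendar period.** No calculation was made for this part. The case rests on the text: time is named as a source of bias, and no listed term represents it.

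**The case against.** The strongest reply is that most of this is inferred from silence. The protocol says coding variation may cause bias, not that it does, and declaring a limitation does not contradict a model. The Cox model is called stratified without its strata being named, so practice strata are not ruled out. Every input to the bias calculation is assumed, and at SD 0.2 the result is only 1.02 to 1.04. For patients entering on 1 January 2009, a time-since-entry scale would already follow calendar time. Practice strata inside age and sex subgroups would be sparse at 36 to 48 adults per practice.

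Much of this is fair, and it limits the point. It does not remove it. The protocol does enumerate its adjustment set, twice, and both lists omit the two sources of bias it names. The unnamed Cox strata cannot safely be read as practice. The only stratification described is by age, sex and intellectual disabilities, and the last cannot divide a cohort in which everyone has them. The time scale is not stated, and later entrants would not be aligned to calendar time.

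Three stronger readings are tempting, and the documents do not support them.

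- *The standard errors ignore clustering.* No variance method is stated, and that is commonly left to an analysis plan. For conditions that vary within practice the effect is also small: with both intraclass correlations at 0.05 (assumed), the design effect is 1 + (m − 1) × 0.05², which is 1.09 at m = 36.2 and 1.12 at m = 48.5.
- *Every physical condition would show a ratio above 1.* This needs positively correlated recording habits for that condition and the outcome.
- *The protocol expects small effects.* It states no expected effect. The values 0.16 and 0.28 are background on epilepsy alone.

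**Conclusion.** The point holds as a mismatch between the bias the protocol names and the adjustment it lists. If the listed set is followed as written, a shared-recording bias stays in the main association wherever practices' habits for the condition and for the outcome are positively correlated. Under the assumed SDs of 0.3 to 0.5 and correlations of 0.5 to 1, the false ratio is about 1.05 to 1.27; the top figure needs perfect correlation. At SD 0.2 it is 1.02 to 1.04, and with uncorrelated habits it vanishes. None of these inputs is in the documents, so this shows what is possible and does not estimate the bias in this study. The calendar-period part is sound in principle but unquantified. Because a better model can be built on the Cox method already chosen, the change should be made.

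**What to change.** In Phase 2:

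1. Name the strata of the Cox model, and stratify the baseline hazard by practice in the main full-cohort models.
2. Add calendar period by splitting follow-up, for example by year.
3. In the Poisson model, include practice (as fixed effects or through conditional Poisson regression) and calendar period. Clustered standard errors alone are not enough.
4. Use the patient-level deprivation index in the practice-stratified models, because the practice-level index is constant within a practice.
5. Report the model without practice strata alongside, and also where subgroups are too sparse for practice strata.

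The confounding section should list the same terms. The cost is protocol and analysis-plan wording, assuming the extract carries a practice identifier and event dates, as registration-based follow-up implies. There is some loss of information: practices with no events or no exposure contrast contribute nothing, and the effect of practice-level deprivation cannot be estimated in the stratified model. That index is listed as a confounder and remains available in the model without practice strata.

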**Appendices**

[figure not shown] appendix-1\_0.pdf

**Grant ID**
